#### 4.1.3 STAGE 1: SAFETY RUN-IN

The original protocol (version 1, dated 12/22/21) specified that approximately six patients (no more than 18, accounting for the possible need for additional dose levels) will be accrued in Stage 1. A single patient will be treated with evorpacept (ALX148) 15 mg/kg weekly, cetuximab (400 mg/m^2 cycle 1 day 1 followed by 250 mg/m^2 weekly), and pembrolizumab (200 mg every 3 weeks), followed by a 48-hour safety observation period prior to treating the next patient. A 48-hour safety observation period will be required between the start of treatment for patients in Stage 1. One cycle will be 21 days. Evorpacept (ALX148) dosing is based on prior phase I data in which no maximum tolerated dose (MTD) was reached alone or in combination (maximum administered dose 15 mg/kg weekly with pembrolizumab and chemotherapy and 15 mg/kg weekly with rituximab and trastuzumab) and treatment was well tolerated. Cetuximab and pembrolizumab dosing is based on standard dosing. Once 6 patients have been enrolled into the study, further accrual to the study will be temporarily halted while the study team reviews the totality of the first-cycle clinical data to determine safety and tolerability of the regimen. The safety review should contain data from patients who have been receiving the regimen for a minimum of one cycle of treatment.

Further enrollment and study treatments will be halted if either of the following occur:

- Any patient experiences death due to an adverse event that is assessed as related to study treatment (by investigator and/or AGICC)
- At least 33% of patients experience a DLT

If these doses are not tolerable (i.e. at least 33% of patients experience a first-cycle DLT, see below), then 3 additional patients will be enrolled in dose level -1 which will comprise the same doses of cetuximab and pembrolizumab with a lower dose of evorpacept (ALX148) (10 mg/kg weekly). The cetuximab dose may be reduced (to 200 mg/m^2 weekly) if DLT(s) are incontrovertibly attributable to cetuximab, after review by AGICC and the Investigators. If no DLTs are observed, dose level -1 will be the recommended Stage 2 dose. If 1 DLT is observed, then additional patients will be enrolled at dose level -1. If, after enrolling additional patients at dose level -1, at least 33% of patients experience a DLT at dose level -1, then 3 patients will be enrolled in dose level -2 which will comprise the same doses of cetuximab and pembrolizumab with a lower dose of evorpacept (ALX148) (5mg/kg weekly). The cetuximab dose may be reduced (to either 200 mg/m^2 weekly or 150 mg/m^2 weekly, depending on the prior cetuximab dose level) if DLT(s) are incontrovertibly attributable to cetuximab, after review by AGICC and the Investigators. In the safety run-in, cetuximab dose adjustments are not allowed unless the DLT(s) is incontrovertibly attributable to cetuximab. If no DLTs are observed, dose level -2 will be the recommended Stage 2 dose. If 1 DLT is observed, then additional patients will be enrolled at dose level -1. If, after enrolling additional patients at dose level -2, at least 33% of patients experience a DLT at dose level -2, the study will end.

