### 1. Dose Levels:

- Evorpaccept (ALX148) dose level (DL) 1: 15 mg/kg weekly; DL -1: 10 mg/kg weekly; DL -2: 5 mg/kg weekly
- Cetuximab DL 1: 250 mg/m^2 weekly; DL -1: 200 mg/m^2 weekly; DL -2: 150 mg/m^2 weekly
- Pembrolizumab DL 1: 200 mg every 3 weeks (no additional dose levels)

2. The desired mechanism of action of cetuximab is to augment phagocytosis via antibody-dependent cellular phagocytosis (ADCP) rather than to modulate the EGFR signaling pathway.

3. No more than 18 evaluable patients will be accrued in Stage 1. A single patient will be treated with evorpacept (ALX148), cetuximab, and pembrolizumab, followed by a 48-hour safety observation period prior to treating the next patient. A 48-hour safety observation period will be required between the start of treatment for patients in Stage 1. Additional patients may be enrolled at lower dose levels if at least 33% of patients experience a first-cycle dose limiting toxicity.
4. If a significant portion of patients in Stage 2 experience AEs meeting dose-limiting toxicity (DLT) criteria as defined in Section 4.1.5, then dose reduction(s) of evorpacept (ALX148) and/or cetuximab for subsequent patients can be considered in discussion with the Investigators and Medical Monitor.
5. A Simon-like 2-stage design will be used. If there are no responses (partial response or complete response) among the first 24 evaluable patients (including patients in both Stage 1 and Stage 2), study enrollment will be stopped for futility. Otherwise, full study enrollment will continue as planned.

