### **Protocol amendment version 2 (dated December 28, 2022)**

During Stage 1 of this study, six patients were administered evorpacept (ALX148) 15 mg/kg, weekly in combination with pembrolizumab and cetuximab. One patient experienced a DLT of grade 5 HLH (see Section 2.3.1) that was assessed as possibly related to ALX148, pembrolizumab and cetuximab and the study was temporarily paused per protocol guidance. Three additional patients had completed the full DLT assessment period (all cycle 1 study treatments) and two additional patients did not complete all cycle 1 doses without reporting a DLT. Protocol amendments included in version 2 (dated December 28, 2022) dictate modification to Stage 1 when the study re-opens to enrollment in response to this event. Stage 1 will evaluate an additional patient cohort (N=3) administered evorpacept (ALX148) dose level -1 (10 mg/kg weekly) and dose level 1 of both cetuximab (400 mg/m^2 cycle 1 day 1 followed by 250 mg/m^2 weekly) and pembrolizumab (200 mg every 3 weeks). If there are no DLTs among these 3 patients, then N=3 additional patients will be enrolled at evorpacept dose level 1 (15 mg/kg weekly) with the same doses of cetuximab and pembrolizumab. If there is one DLT among the initial 3 patients enrolled at evorpacept (ALX148) dose level -1 (evorpacept 10 mg/kg), a further 3 patients will be enrolled at that dose level. Escalation to dose level 1 (evorpacept 15 mg/kg) should only be permitted if either 0 of 3 or 1 of 6 patients experience a DLT at evorpacept (ALX148) dose level -1. This follows a standard '3+3' study design at

ALX148 dose level -1 (evorpacept 10 mg/kg) upon re-initiation of the study. Consistent with protocol version 1, the study will proceed to Stage 2 at doses where less than 33% of patients experience a first-cycle DLT. See Figure 6 for additional details on the management of Stage 1 under protocol version 2. Note that in the event of a further DLT in 1 of 3 patients at evorpacept (ALX148) dose level 1 (evorpacept 15 mg/kg) i.e., 2 of 7 patients treated at dose level 1 (including N=4 patients treated under protocol version 1 dated 12/22/21), a complete safety evaluation including assessment of late onset toxicities should be reviewed by the data safety monitoring committee (DSMC) prior to proceeding to Stage 2. This DSMC review would be in addition to the DSMC review after N=12 patients in Stage 2 have been treated for at least one cycle as noted in Section 4.1.1.

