## **Dose, administration, and premedication**

### *Evorpaccept (ALX148) (per the Investigator's Brochure)*

- Dose: 15 mg/kg day 1, 8, and 15 every 21 days
- Administration: Administer infusion solution intravenously over 60 minutes  $\pm$  10 minutes. The use of an infusion pump is the preferred method of administration to ensure accurate delivery of the investigational product, but gravity drips are allowed.
- Pre-medication: none required
- Route of administration: intravenous
- Starting dose and dose escalation: not applicable
- Dose adjustments/modifications/delays: see Appendix 1
- Duration of therapy: Patients in both the safety run-in and dose expansion stages will continue to receive study therapy until disease progression according to RECIST v1.1, unacceptable toxicity, death, patient or physician decision to withdraw, or pregnancy, whichever occurs first. Criteria in which patients in all cohorts may continue treatment after radiographic progression are detailed in Section 4.1.2.
- Tracking of dose: not applicable

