### 12.1.2 DOSE LEVELS

#### Evorpaccept (ALX148)

- Dose level 1: 15 mg/kg weekly
- Dose level -1: 10 mg/kg weekly
- Dose level -2: 5 mg/kg weekly

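### One DLT at evorpacept dose level -2 (5 mg/kg) sends the additional patients to dose level -1 (10 mg/kg), and the next sentence assumes dose level -2

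*Protocol*

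**What the plan says.** Section 4.1.3 of the protocol sets out step-down rules for the safety run-in. The levels are defined in the dose-level note to the study schema ("DL -1: 10 mg/kg weekly; DL -2: 5 mg/kg weekly") and again in Section 12.1.2.

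- **Dose level -1.** Three patients are enrolled. No DLT makes it the recommended dose. One DLT leads to more patients at the same level. If the rate after that is too high, the next level opens: "at least 33% of patients experience a DLT at dose level -1, then 3 patients will be enrolled in dose level -2".
- **Dose level -2.** The scheme is repeated. No DLT makes it the recommended dose. For one DLT, the instruction and the start of the following sentence read: "additional patients will be enrolled at dose level -1. If, after enrolling additional patients at dose level -2, at least 33% of patients". The second sentence ends the study if that proportion have a DLT at dose level -2.

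The section introduces these rules as coming from version 1 ("The original protocol (version 1, dated 12/22/21) specified that approximately six patients"). The version 2 text that follows sets a 3+3 scheme at dose level -1 and a possible return to dose level 1. It keeps the condition that "the study will proceed to Stage 2 at doses where less than 33% of patients experience a first-cycle DLT", and says nothing about dose level -2.

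**The concern.** The dose level -2 branch contradicts itself in consecutive sentences: one enrols the additional patients at dose level -1, the other assesses the DLT rate after enrolling them at dose level -2.

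The literal instruction also goes in the unsafe direction. Dose level -2 is reached only because dose level -1 was too toxic, so a DLT at 5 mg/kg would send new patients back to 10 mg/kg. Meanwhile dose level -2 would gain no further patients, and its own acceptability would remain open.

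The recommended dose is a primary endpoint (Section 3). The run-in has already had a grade 5 DLT. That event occurred at 15 mg/kg and does not make a misreading more likely, but it is a reason for the dose-assignment rules to be unambiguous.

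**Working it through.** The protocol gives no figure to reproduce here. The check is a comparison of the text, followed by simple arithmetic.

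**1. The two branches of Section 4.1.3 side by side**

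| Outcome | Dose level -1 branch | Dose level -2 branch |
|---|---|---|
| No DLT | -1 is recommended | -2 is recommended |
| One DLT: more patients at | -1 | **-1** |
| Next sentence assesses patients added at | -1 | -2 |
| At least 33% with a DLT | open -2 | study ends |

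Only the bold cell breaks the pattern.

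**2. Dose consequence.** Section 12.1.2 gives "Dose level -1: 10 mg/kg weekly" and "Dose level -2: 5 mg/kg weekly". Section 6.1.2 gives three infusions per cycle ("15 mg/kg day 1, 8, and 15 every 21 days" at dose level 1).

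- Ratio: 10 / 5 = 2.
- Per 21-day cycle: 3 × 10 = 30 mg/kg against 3 × 5 = 15 mg/kg.

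**3. Where dose level -2 is left.** One DLT in three is 1/3 = 33.3%.

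- The no-DLT rule is not met.
- The study-ending rule applies only after patients have been added at dose level -2, and none would have been.
- Stage 2 requires a rate below 33%, and 33.3% is not below it.

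With the level corrected, and assuming three more patients (no number is stated), no further DLT gives 1/6 = 16.7%, which is acceptable. One further DLT gives 2/6 = 33.3%, and the study ends.

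**4. Chance of reaching the branch.** The protocol gives no DLT rates, so those below are assumptions.

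Once dose level -2 is open, P(exactly 1 of 3) = 3p(1 − p)²:

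- p = 0.1: 0.243
- p = 0.2: 0.384
- p = 0.3: 0.441

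From the opening of dose level -1, using the version 2 3+3 rule, P(leave -1) = P(at least 2 of 3) + P(1 of 3) × P(at least 1 of the next 3):

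- p = 0.2: 0.104 + 0.384 × 0.488 = 0.291
- p = 0.3: 0.216 + 0.441 × 0.657 = 0.506

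Multiplying the two steps:

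| Rate at -1 | Rate at -2 | Chance of reaching the branch |
|---|---|---|
| 0.2 | 0.1 | 0.291 × 0.243 = 0.071 |
| 0.2 | 0.2 | 0.291 × 0.384 = 0.112 |
| 0.3 | 0.1 | 0.506 × 0.243 = 0.123 |
| 0.3 | 0.2 | 0.506 × 0.384 = 0.194 |
| 0.3 | 0.3 | 0.506 × 0.441 = 0.223 |

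The lower end depends on the rate assumed at dose level -1. With 10% at both levels, P(leave -1) = 0.028 + 0.243 × 0.271 = 0.094, and 0.094 × 0.243 = 0.023.

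**The case against.** The case for giving this little weight has four parts.

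- **Status of the text.** The rule is presented as version 1 text, and version 2 refers to Figure 6 for managing Stage 1. That figure was not available and may show the correct path. This stands as a limit: the wording conflict is certain, but whether the clause governs current enrolment is less so. Against that, the rule is in the body of Section 4.1.3 rather than in a change log. The visible version 2 text does not withdraw it, and dose level -2 is still listed.
- **The text corrects itself.** The next sentence names dose level -2, and the parallel branch shows the pattern. This is fair. Harm would need staff to act on one sentence and overlook the other.
- **Other safeguards.** Section 4.1.3 halts enrolment and treatment when at least 33% of patients have a DLT. Read per dose level, 1 of 3 would trigger it, although the denominator is not stated. Note 3 to the schema speaks of additional patients at lower levels, and the DSMC reviews all SAEs and can suspend the trial (Section 10.1.5). These make an actual misassignment less likely. However, a halt only pauses accrual; it does not say which dose comes next or settle 1 of 3 at dose level -2.
- **The probabilities rest on assumed rates.** They also join the version 2 rule at dose level -1 to the version 1 rule at dose level -2. Both points are correct. The figures show that the branch is not remote at moderate DLT rates, and nothing more.

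**Conclusion.** The concern holds. The dose level -2 rule is wrong as written: its two sentences name different levels, and the literal instruction doubles the evorpacept dose at a level already left for toxicity. It is very probably a copy of the dose level -1 clause, and the intended rule is not in doubt.

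The branch has a 24% to 44% chance once dose level -2 is open (assumed DLT rate 10% to 30%). From the opening of dose level -1 the chance is about 7% to 22%, with 20% to 30% assumed at dose level -1 and, at dose level -2, 10% up to that same rate. It falls to about 2% if both rates are 10%. None of these is a probability of harm.

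The correction should be made, because this is an operative dosing rule that feeds a primary endpoint. No analysis or sample size is affected. Confidence is high on the conflict in the text; the contents of Figure 6 remain unknown.

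**What to change.** In the dose level -2 branch of Section 4.1.3, change the level at which additional patients are enrolled after one DLT from -1 to -2. Check that Figure 6, if it covers dose level -2, agrees. The cost is a single-digit correction in the next amendment.

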### **Protocol amendment version 2 (dated December 28, 2022)**

During Stage 1 of this study, six patients were administered evorpacept (ALX148) 15 mg/kg, weekly in combination with pembrolizumab and cetuximab. One patient experienced a DLT of grade 5 HLH (see Section 2.3.1) that was assessed as possibly related to ALX148, pembrolizumab and cetuximab and the study was temporarily paused per protocol guidance. Three additional patients had completed the full DLT assessment period (all cycle 1 study treatments) and two additional patients did not complete all cycle 1 doses without reporting a DLT. Protocol amendments included in version 2 (dated December 28, 2022) dictate modification to Stage 1 when the study re-opens to enrollment in response to this event. Stage 1 will evaluate an additional patient cohort (N=3) administered evorpacept (ALX148) dose level -1 (10 mg/kg weekly) and dose level 1 of both cetuximab (400 mg/m^2 cycle 1 day 1 followed by 250 mg/m^2 weekly) and pembrolizumab (200 mg every 3 weeks). If there are no DLTs among these 3 patients, then N=3 additional patients will be enrolled at evorpacept dose level 1 (15 mg/kg weekly) with the same doses of cetuximab and pembrolizumab. If there is one DLT among the initial 3 patients enrolled at evorpacept (ALX148) dose level -1 (evorpacept 10 mg/kg), a further 3 patients will be enrolled at that dose level. Escalation to dose level 1 (evorpacept 15 mg/kg) should only be permitted if either 0 of 3 or 1 of 6 patients experience a DLT at evorpacept (ALX148) dose level -1. This follows a standard '3+3' study design at

ALX148 dose level -1 (evorpacept 10 mg/kg) upon re-initiation of the study. Consistent with protocol version 1, the study will proceed to Stage 2 at doses where less than 33% of patients experience a first-cycle DLT. See Figure 6 for additional details on the management of Stage 1 under protocol version 2. Note that in the event of a further DLT in 1 of 3 patients at evorpacept (ALX148) dose level 1 (evorpacept 15 mg/kg) i.e., 2 of 7 patients treated at dose level 1 (including N=4 patients treated under protocol version 1 dated 12/22/21), a complete safety evaluation including assessment of late onset toxicities should be reviewed by the data safety monitoring committee (DSMC) prior to proceeding to Stage 2. This DSMC review would be in addition to the DSMC review after N=12 patients in Stage 2 have been treated for at least one cycle as noted in Section 4.1.1.

**Figure 6. Modification to Stage 1 with Protocol Version 2 (dated December 28, 2022)**

[figure not shown]

Abbreviations: DL, dose level; DLT, dose-limiting toxicity; DSMC, data safety monitoring committee.

\*Includes N=4 patients treated with evorpaccept (ALX148) dose level 1 under protocol version 1 (dated 12/22/21) that are DLT evaluable (including 1 DLT [HLH]).

\*\* In the event of a further DLT in 1 of 3 patients at evorpaccept (ALX148) dose level 1 (evorpaccept 15 mg/kg) i.e., 2 of 7 patients treated at dose level 1 (including N=4 patients treated under protocol version 1 dated 12/22/21), a complete safety evaluation including assessment of late onset toxicities should be reviewed by the data safety monitoring committee (DSMC) prior to proceeding to Stage 2. This DSMC review would be in addition to the DSMC review after N=12 patients in Stage 2 have been treated for at least one cycle as noted in Section 4.1.1.

A maximum of 18 patients will be enrolled in Stage 1. Upon determination of the safety and tolerability of the treatment regimen, including determination of the evorpaccept (ALX148) RD (and cetuximab RD if needed), the study will proceed to Stage 2. Only after the regimen has been determined to be safe and tolerable can the dose expansion phase be initiated (Stage 2).

Given the potential for late-onset toxicities, adverse event data will be collected for all patients in Stage 1 for 90 days after Cycle 1 Day 1. If additional DLT(s) are encountered during this extended monitoring period after the study has proceeded to Stage 2, then further enrollment in Stage 2 will be halted until discussion with the Investigators and Medical Monitor. If this occurs, the doses used in Stage 2 may be modified after discussion with the Investigators and Medical Monitor.

---

#### **4.1.4 STAGE 2: DOSE EXPANSION**

Forty-two patients will be enrolled and treated with the evorpacept (ALX148) RD, cetuximab (400 mg/m^2 day 1 of week 1 followed by 250 mg/m^2 weekly, unless a different RD is determined), and pembrolizumab (200 mg every 3 weeks). One cycle will be 21 days. There will be two cohorts – Cohort A and Cohort B. Enrollment will not occur by randomization and instead will occur based on Investigator and patient preference and slot availability.

If a significant portion of patients in Stage 2 experience AEs meeting DLT criteria as defined in Section 4.1.5, then dose reduction(s) of evorpacept (ALX148) and/or cetuximab for subsequent patients can be considered in discussion with the Investigators and Medical Monitor.

Patients in Cohort A will provide a fresh pretreatment biopsy sample and an on-treatment biopsy sample at C3D1 ( $\pm 3$  days). Prior to the pre-treatment biopsy, patients must sign the Informed Consent Form and all other described screening evaluations (Section 8.2.1 – “Screening Assessments to Determine Eligibility”) must be completed and reviewed by the treating clinician to confirm that all eligibility criteria are met. While the acceptable window for the C3D1 biopsy is  $\pm 3$  days, it is preferred for the biopsy to occur following all treatments on C3D1. The date and time of the biopsies will be documented. In Cohort A, archival tissue may not be used in place of a fresh pre-treatment biopsy. Patients in Cohort B will not undergo any study-related biopsies. When available, archival tissue will also be obtained for analysis for patients in both Cohort A and Cohort B. Other than biopsies, there are no differences between Cohort A and Cohort B (both receive the same treatment and study events). Details for handling of these samples including processing, storage, and shipment will be provided in the Laboratory Manual.

In rare circumstances, if there are no available spots in Cohort B and if a patient is motivated to participate and the Investigator judges that the risk associated with the biopsy is not appropriate for a research setting or the patient refuses biopsy, after consultation with the AGICC’s medical monitor the patient may be allowed on study without a fresh biopsy. Similarly, for a subject in Cohort A, if the Investigator judges the risk for the pre- or on-treatment biopsy to be unacceptable in a research setting eg, based on complications during a previous procedure, use of blood thinning medications, or inaccessible tumor, or the patient refuses, a subject should not undergo the pre- or on-treatment biopsy and the patient will be allowed to enroll on or remain

on the study. If a patient initially assigned to Cohort A is unable to undergo both the pretreatment and on-treatment biopsies due to medical reasons or patient refusal, an additional patient may be enrolled in Cohort A (to achieve N=23 patients who underwent pretreatment and on-treatment biopsies).

Patients will undergo imaging of the chest, abdomen, and pelvis every 9 weeks for evaluation of response using RECIST v1.1 and iRECIST. Patients in both the safety run-in and dose expansion stages will continue to receive study therapy until disease progression according to RECIST v1.1 (Appendix 2), unacceptable toxicity, death, patient or physician decision to withdraw, or pregnancy, whichever occurs first. The maximum duration of pembrolizumab is 35 cycles. There is no maximum duration of evorpaccept (ALX148) or cetuximab. Criteria for continuation of treatment beyond RECIST v1.1-defined progression is listed above in Section 4.1.2. The time from first patient enrollment until end of follow-up is expected to take approximately 48 months (24 months for enrollment/treatment and an additional 24 months for survival follow-up).

---

#### 4.1.5 DOSE-LIMITING TOXICITIES

Adverse events (AEs), serious adverse events (SAEs), and clinically significant laboratory values that occur during the study and considered related to any of the study drugs will be regularly evaluated to determine whether continued dosing would potentially compromise the safety of future subjects. The severity of adverse events will be graded according to CTCAE version 5.0. The following constitute the definition of DLT in this study:

- Hematologic:
  - Grade 4 neutropenia lasting >7 days
  - Febrile neutropenia (defined as neutropenia  $\geq$  Grade 3 and a single body temperature  $>38.3^{\circ}\text{C}$  or a sustained temperature of  $\geq 38^{\circ}\text{C}$  for more than one hour)
  - Grade  $\geq 3$  neutropenia with infection
  - Grade 3 thrombocytopenia associated with clinically significant bleeding
  - Grade 4 thrombocytopenia
  - Grade  $\geq 3$  hemophagocytic lymphohistiocytosis
- Non-hematologic:
  - AST or ALT  $> 3$  x upper limit of normal (ULN) AND total bilirubin  $> 2$  x ULN, unless clear evidence of biliary obstruction exists
  - For patients with hepatic metastases, AST or ALT  $> 8$  x ULN or AST or ALT  $> 5$  x ULN for  $\geq 14$  days
  - Any Grade 2 pneumonitis that does not resolve to Grade  $\leq 1$  within 3 days of the initiation of maximal supportive care
  - Grade  $\geq 3$  toxicities, with the exception of the following:

- Grade 3 nausea/vomiting or diarrhea <72 hours with adequate antiemetic and other supportive care
- Grade 3 pain, rash, or constipation if duration is < 7 days
- Grade 3 fatigue if duration is < 7 days
- Grade  $\geq$  3 electrolyte abnormality that lasts < 72 hours, is not clinically complicated, and resolves spontaneously or responds to conventional medical interventions
- Grade  $\geq$  3 amylase or lipase that is not associated with symptoms or clinical manifestations of pancreatitis
- Grade  $\geq$  3 hypertension that recovers to Grade 2 within 5 days
- Delay by more than 2 weeks in receiving the next scheduled dose due to persisting toxicities attributable to evorpaccept (ALX148)
- In addition, clinically significant or persistent Grade 2 toxicities may be considered a DLT following review by AGICC and the Investigators.
  - A clinically significant laboratory value is one that indicates a new disease process, an exacerbation or worsening of an existing condition, or requires further action(s) to be taken

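### The hematologic DLT list in 4.1.5 has no item for grade 3–4 hemolysis, so a related case is not a DLT in itself and may go uncounted in the Stage 1 dose rules

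*Protocol*

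**What the plan says.** Section 4.1.5 defines dose-limiting toxicity by a list, introduced by "The following constitute the definition of DLT in this study".

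- **Hematologic items:** three for neutropenia (prolonged grade 4, febrile, or grade ≥3 with infection), two for thrombocytopenia (one of them "Grade 3 thrombocytopenia associated with clinically significant bleeding", the other grade 4), and grade ≥3 HLH. There is no item for anemia or hemolysis.
- **Non-hematologic items:** these include AST or ALT above 3 × ULN together with bilirubin above 2 × ULN, and a general clause for grade ≥3 "toxicities, with the exception of the following".
- **Other items:** a delay of more than two weeks to the next dose from persisting toxicity attributed to evorpacept, and a discretionary clause: "In addition, clinically significant or persistent Grade 2 toxicities may be considered a DLT following review by AGICC and the Investigators".

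The counts feed the Stage 1 rules in 4.1.3, under the version 2 amendment. Escalation from dose level -1 to dose level 1 "should only be permitted if either 0 of 3 or 1 of 6 patients experience a DLT" at dose level -1. In general, "the study will proceed to Stage 2 at doses where less than 33% of patients experience a first-cycle DLT". A further DLT among the new dose level 1 patients, making "2 of 7 patients treated at dose level 1", requires a DSMC review first. A DLT found later, within 90 days of Cycle 1 Day 1, halts Stage 2 enrollment pending discussion.

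**The concern.** Hemolysis is a risk the protocol itself anticipates. Section 2.2.3 says red cells undergo dose-dependent phagocytosis under SIRPα/CD47 blockade and that anemia has limited other anti-CD47 agents. Section 8.2.1 asks for a hemolysis work-up to be considered if unanticipated anemia develops. Section 12.1.3 says evorpacept may cause hematologic toxicity and gives hemolytic anemia its own management table, with permanent discontinuation of study treatments at both grade 3 and grade 4.

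The DLT list does not match that table. Grade 4 thrombocytopenia is a DLT, yet 12.1.3 lets treatment restart with evorpacept one level lower. Grade 3–4 hemolysis ends treatment, yet is not listed. The discretionary clause would let a persistent grade 2 hemolysis be called a DLT, but it does not name grades 3 and 4.

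At stake are dose decisions taken on three to seven patients, where a single event decides the next step.

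**Working it through.** **Step 1. Is hemolysis hematologic in this protocol?** Yes, in two places. The hemolytic anemia table sits in 12.1.3, the section on hematologic toxicity. The retreatment criteria in 12.1.1 list hemolysis on a separate line from non-hematologic toxicities.

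**Step 2. Does any item in 4.1.5 name it?** No hematologic item does. The grade ≥3 clause is printed under the non-hematologic items, so on the plain reading it does not reach hemolysis.

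**Step 3. Which items might catch a case incidentally?**

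| Route | What it needs |
|---|---|
| Delay of more than two weeks (4.1.5) | Attribution to evorpacept, and reading a permanent stop as a delay to the next dose |
| Grade ≥3 HLH (4.1.5; note e in 12.1.3) | HLH as the accompanying or underlying event |
| Liver item (4.1.5) | AST or ALT above 3 × ULN and bilirubin above 2 × ULN, without clear biliary obstruction |
| Grade ≥3 bilirubin (grades in 12.1.6) | Bilirubin above 3 × ULN with a normal baseline; bilirubin is not among the exceptions |
| Other grade ≥3 organ toxicity | A separate non-hematologic consequence |

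The hemolysis table defines grade 3 by the need for transfusion or medical intervention. A patient can meet that without meeting any row above.

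**Step 4. What does one uncounted case change?** The inputs are the rules in 4.1.3. Dose level 1 starts from 1 DLT in 4 evaluable patients and adds 3, which gives 7.

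| Dose level | Case not counted | Case counted | Change in prescribed action |
|---|---|---|---|
| -1 | 0/3 | 1/3 | Three more patients at this level instead of escalation |
| -1 | 1/6 = 16.7% | 2/6 = 33.3% | Escalation barred |
| 1 | 1/7 = 14.3% | 2/7 = 28.6% | Extra DSMC review required |
| 1 | 2/7 = 28.6% | 3/7 = 42.9% | Fails the under-33% rule |

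The protocol's own 2 of 7 is 28.6%, below 33%, which agrees with its choice to require review there rather than stop.

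**Step 5. Scale.** The documents give no hemolysis rate, so the rates here are assumptions. For a per-patient DLT probability p, the chance of meeting the dose level -1 escalation rule (0 of 3, or 1 of 3 followed by 0 of 3) is

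(1 − p)³ + 3p(1 − p)² × (1 − p)³.

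At p = 0.20 this is 0.512 + 0.6 × 0.32768 = 0.709. Adding 1, 2 or 5 percentage points for hemolysis in patients who would otherwise have no counted DLT gives:

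| Assumed counted DLT rate | Hemolysis not counted | +1 point | +2 points | +5 points |
|---|---|---|---|---|
| 10% | 0.906 | 0.889 | 0.871 | 0.814 |
| 20% | 0.709 | 0.687 | 0.665 | 0.600 |
| 30% | 0.494 | 0.474 | 0.454 | 0.396 |

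The largest fall in the table is 0.709 − 0.600 = 0.109.

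**The case against.** **The grade ≥3 clause might be meant to cover everything.** Against this, it would make the bleeding condition on grade 3 thrombocytopenia and the seven-day condition on grade 4 neutropenia pointless. That argument favors the plain reading but does not prove it, because the list already overlaps itself. For patients with hepatic metastases, transaminases must exceed 8 × ULN, or 5 × ULN for at least 14 days. Yet 12.1.6 grades anything above 5 × ULN as grade 3 when baseline is normal, and transaminases are not excepted. The drafting is loose, and a safety team might well treat grade 4 hemolysis as a DLT whatever the layout. What stands is that the text does not tell them to.

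**The event would be seen anyway.** This is largely right. Section 4.1.5 has related adverse events evaluated regularly, and 8.3.6 requires SAE submission within 24 hours. Stage 2 opens only once the regimen is judged safe and tolerable (4.1.3). The DSMC reviews all SAEs and can suspend the trial (10.1.5), and it meets after 12 Stage 2 patients (4.1.1). A related death halts the study. The Stage 2 dose-reduction provision in 4.1.4 is discretionary, so little turns on the definition there.

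**The risk is low.** Evorpacept's inactive Fc was designed to limit cytopenias (2.2.3). Patients with a prior hemolytic transfusion reaction or autoimmune hemolytic anemia are excluded (5.2). The evorpacept data in 2.3.1 list no hemolysis, and grade ≥3 anemia in 2% with pembrolizumab. This limits the size of the concern without closing the gap.

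**Stronger readings.** A reader might infer that grade 3–4 hemolysis can never count as a DLT; the routes in the first working table show otherwise. A reader might also infer that any event ending treatment must be a DLT. The protocol does not work that way: grade 2 HLH also ends treatment (12.1.12) and is not an automatic DLT.

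**Conclusion.** The gap is real but narrow. As printed, a related grade 3–4 hemolysis is not a DLT in itself, and none of the incidental routes guarantees that it is counted. An uncounted case could change the prescribed action under the dose level -1 rule, the 2-of-7 DSMC trigger and the under-33% rule, and could miss the 90-day halt.

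The likely effect is small. Under the assumed rates of 1 to 5 points for hemolysis and 10% to 30% for other DLTs, the chance of escalating from dose level -1 is overstated by roughly 0.02 to 0.11. No event probability is claimed, because the documents supply none. The documents do not support saying that such an event would escape safety oversight, only that the formal counts need not include it.

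The conclusion rests on reading the grade ≥3 clause as confined to the non-hematologic items, where it is printed. If the sponsor intends it to cover all toxicities, the text should say so, and the neutropenia and thrombocytopenia conditions would need revisiting.

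**What to change.** Add one bullet to the hematologic DLTs in 4.1.5: *Grade ≥3 hemolysis/hemolytic anemia related to study drug.*

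The cost is one line in an amendment, with no new data or visits. The downside is that slightly more events may count as DLTs, so escalation could be a little slower.
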